## USE OF ADVANCED, NON-INVASIVE DIAGNOSTIC METHODOLOGY FOR EARLY DIAGNOSIS OF SKIN CANCER IN IMPROVING THERAPEUTIC AND ECONOMIC-MANAGEMENT OF CLINICAL PRACTICE.

### **Background and rationale:**

The clinical diagnosis of cutaneous melanoma is complex. The aim of this project is to assess the effectiveness of the systematic integration of reflectance confocal laser microscopy (RCM) into the skin neoplasms diagnostic/clinical pathway.

Two instruments will be assessed:

- fixed head RCM (VivaScope 1500), capable of producing a virtual, non-invasive skin cancer in-vivo biopsy
- manual RCM (VivaScope 3000), for rapid screening of patients at high risk of melanoma for especially for early diagnosis of thin melanomas.

The evaluation of the cost-utility ratio of the device integration will be calculated based on a model specifically designed, developed and tested based on study data, within the network of the 3 collaborating hospitals (in a single Italian Region). The aim is to therefore evaluate whether the proposed skin cancer triage system is useful for reducing waiting lists and costs related to surgery and histopathology.

Skin neoplasms are the most common cancers in humans and represent substantial social costs for diagnosis and treatment. Due to the difficulty in arriving to a diagnosis based on clinical and dermoscopic evaluation only, a ratio of about 30 benign lesions excised for every melanoma identified has been calculated. RCM allows a non-invasive virtual biopsy of the tumor and a more accurate diagnosis thanks to the visualization of the skin lesion at a cytological resolution level. However, the advantage in clinical practice for patients and in economic terms of the implementation of this non-invasive technique as a pre-surgical diagnostic step has not yet been demonstrated. RCM may lead to the early diagnosis of skin tumors otherwise unable to be diagnosed in clinical and dermoscopy evaluations, potentially offsetting the enormous costs of treating advanced disease and considerably reducing the number of unnecessary excisions thus, representing a substantial economic advantage for health care.

RCM is a rapid, inexpensive and single-operator tool which will be added to the diagnostic triage. The main objective of the project is to assess the impact of the systematic application of RCM in a skin cancer triage, in terms of the number of unnecessary excisions, histopathological examinations and overall health costs.

Of interest, particular attention will be paid to the dermatological triage with RCM integration of the head / neck sites. Pigmented spots are often observed in the head / neck area, which are often the font of a high rate of dermatological consultation requests, both for diagnostic evaluation of suspicious lesions and aesthetic treatments. Among these lesions, differential diagnosis between benign and malignant lentigos is challenging.

Improper treatment (cryotherapy, laser, radiofrequency, etc.) of an unidentified/misdiagnosed lentigo maligna (melanoma in situ) can induce progression into invasive melanoma, with worsening prognosis. As the evaluation of equivocal lesions is often difficult with dermoscopy alone, a biopsy is usually performed for diagnostic or preoperative planning motives. RCM has been successfully used for in vivo characterization of flat skin facial lesions by enabling the exploration of morphological and architectural lesion aspects suggestive of malignancy. Based on preliminary data available in literature, RCM may potentially positively impact not only healthcare costs, but also surgical planning,

which are especially important for this specific skin topographic area, given the important aesthetic impact of facial surgery.

Finally, the effectiveness of the integration of RCM to the clinical practice in non-melanoma malignancies diagnostics, particularly for basal cell carcinoma will also be assessed. Basal cell carcinoma represents the most common malignant neoplasm in Caucasian and Italian populations (AIRTUM data) and has a significant impact in health management and related National Health System costs. Recently, RCM has been shown to have very high sensitivity and specificity for basal cell carcinoma diagnosis and has therefore been adopted in pre- and intra-operative management of basal cell carcinomas surgical margins verifications, particularly for areas at high risk of local recurrence.

### **Scope of the Project**

#### **Principal Objective**

- Evaluate cost-benefit deriving from the presumed reduced number of unnecessary excisions given the accuracy of diagnosis with RCM.
- develop and test a regional triage system for skin cancers based on a radial hospital network model with the systematic integration of RCM into current clinical practice.
- Evaluate diagnostic sensitivity and specificity in screening patients at high risk of skin cancer with the use of the manual RCM tool.

Experimental design 1 aims at a reduction of over 30% of unnecessary excisions, with less than 2% of melanoma delayed

diagnosis (compared with dermoscopy delayed melanoma diagnosis ranging from 7.6 to 16.2%, for digital monitoring (10)),

and with no tumors thicker than 0.5 mm delayed.

#### **Secondary Objectives**

- Evaluate diagnostic accuracy of lentigo maligna with different clinical-instrumental algorithms.
- Define which RCM features distinguish lentigo maligna from benign facial macules, such as solar lentigo, freckles, actinic keratoses and seborrheic keratoses, and to develop an easy-to-use diagnostic algorithm.
- Evaluate the accuracy of basal cell carcinoma diagnosis with RCM.
- Analyze and compare the difference of costs of diagnosis with RCM compared to standard histological examination.
- Compare the time required to perform RCM compared to standard histological examination.

Hypothesis to be tested: the advantage of the integration of RCM to the current clinical-diagnostic pathway (clinical-dermoscopic). Outcomes will be measured in terms of the early diagnosis (number of unnecessary excisions), diagnostic safety (number of melanomas diagnosed), and cost-benefit / efficacy calculation based on the drug model. economic developed within the studio.

### **Design and description of the study**

This is a prospective randomized 2-arm study (performed in 3 hospitals). Consecutive patients with at least 1 lesion suspicious of melanoma (following clinical and dermoscopy evaluation) will be enrolled. Patients will be randomized to the standard therapeutical care ("Clinical and dermoscopy evaluation only") or standard therapeutical care + RCM integration ("RCM evaluation + clinical and dermoscopy evaluation") following identification of a suspicious lesion during the standard therapeutical care.

The main objective is to evaluate the safety of the integration of RCM (diagnostic identification of melanomas) and cost-effectiveness in terms of the comparison of the number of excisions needed to identify 1 melanoma (including the follow-up period). A cost-utility model will be developed to quantify the impact of the proposed triage system on health care costs and diagnostic effectiveness. This model will be tested on the study population.

Patients will be selected consecutively among patients with suspected skin cancer.

Randomization will be allocated at a 1:1 ratio and patients will be allocated to the “RCM evaluation + clinical and dermoscopy evaluation” or “Clinical and dermoscopic evaluation only” following standard therapeutic care; patients allocated to “Clinical and dermoscopic evaluation only” will likely require immediate biopsy for diagnosis, whereas clinicians of patients allocated to the “RCM evaluation + clinical and dermoscopy evaluation” can decide based on RCM evaluation whether to excise the lesion or refer the patient to subsequent digital follow up. Lesions referred to follow-up will be monitored for at least 6 months, and excised if significant changes are observed on dermoscopy.

In detail, the therapeutic-diagnostic pathway for each study arm are as follows:

a) "RCM evaluation + clinical and dermoscopy evaluation": following routine therapeutic care (clinical-dermoscopic examinations) clinicians of patients with suspicious lesions (at least one major or minor clinical and / or dermoscopic criterion for malignancy, as per inclusion / exclusion criteria) will be able to evaluate the lesions with RCM. A clinical decision (removal or digital dermoscopic follow-up) will be made based on the RCM evaluation.

b) "Clinical and dermoscopic evaluation only": following routine therapeutic care (clinical-dermoscopic examinations) clinicians of patients with suspicious lesions (at least one major or minor clinical and / or dermoscopic criterion for malignancy, as per inclusion / exclusion criteria), will make a clinical decision (removal or digital dermoscopic follow-up) without RCM evaluation.

Each participating center will be responsible for its own case history and clinical decisions. Each center will take care of the collection and storage of data. At interim analysis (18 months) collected data and preliminary results will be evaluated collectively and discussed. The investigators at the participating centers have high-level therapeutic-diagnostic pathways in place, as documented by the numerous publications produced by these centers, however, in case of significant discrepancies among the interim clinical performance data, or if requested by individual investigators, some cases may be evaluated independently by other investigators in order to verify diagnostic agreement. These cases may derive either from direct indications from the investigators or randomly selected from the collected cases.

Images will be anonymized and only essential clinical data (sex / age, any significant present or past pathologies) will be provided to the other evaluators.

The definition of the head / neck lesion subset is as follows:

1. Malignant macules with histological diagnosis of melanoma;
2. Benign macules with histological diagnosis of actinic keratoses, solar lentigos, lichen planus-like keratosis, seborrheic keratoses, freckles and junctional / compound / dermal nevi;
3. Benign macules not subjected to biopsy and with clear and defined parameters of clinical, dermoscopic and confocal microscopy benignity;

The main outcome will be the rate of malignant lesions identified within the "RCM evaluation + clinical and dermoscopy evaluation" compared to "Clinical and dermoscopic evaluation only" study arms.

Sensitivity, specificity, diagnostic accuracy, odds ratios (OR) with the 95% confidence interval will be evaluated. Several algorithms will be developed for the diagnosis of lentigo maligna in consecutive head / neck injuries. In particular, the positive and negative predictive values for each individual parameter analyzed will be measured and the combination of parameters capable of increasing diagnostic accuracy and reducing the number of unnecessary excisions, will be identified.

RCM features will be systematically analyzed to distinguish lentigo maligna from benign facial lentigos.

The time required for the assessment of face / neck injuries will be calculated and compared within the two groups.

The subgroup of non-melanocytic malignant lesions should include consecutive cases defined as:

1. Carcinomatous neoformations with histological diagnosis of basal cell carcinoma
2. Carcinomatous neoformations with histological diagnosis of squamous cell carcinoma
3. Benign neoformations with histological diagnosis of actinic keratoses, solar lentigos, lichen planus-like keratosis, seborrheic keratoses, ephelides and junctional / compound / dermal nevi.
4. Benign neoformations not subjected to histological analysis and with clear and defined parameters of clinical, dermoscopic and RCM benignity.

The main result is to evaluate the rate of histologically confirmed, excised basal cell carcinomas detected in the "RCM evaluation + clinical and dermoscopy evaluation" compared to "Clinical and dermoscopic evaluation only" study arms.

Sensitivity, specificity, diagnostic accuracy, odds ratios (OR) with the 95% confidence interval will be evaluated. Finally, the differences between the time, technical and human resources required within the "RCM evaluation + clinical and dermoscopy evaluation" compared to "Clinical and dermoscopic evaluation only" study arms.

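### The head/neck and non-melanocytic subsets are called consecutive but are closed lists based largely on final histology, each leaving out a class of malignancy, so the head/neck malignancy rate is really a melanoma rate

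*Protocol*

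**What the plan says.** All of this stands in the protocol, under Design and description of the study.

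**Head/neck subset.** Three classes are listed:
- "Malignant macules with histological diagnosis of melanoma"
- "Benign macules with histological diagnosis of actinic keratoses, solar lentigos, lichen planus-like keratosis, seborrheic keratoses, freckles and junctional / compound / dermal nevi"
- "Benign macules not subjected to biopsy and with clear and defined parameters of clinical, dermoscopic and confocal microscopy benignity"

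Directly after the list comes the outcome, compared between the two arms: "The main outcome will be the rate of malignant lesions identified within". Sensitivity, specificity, accuracy and odds ratios are then planned, with predictive values for each parameter. On sampling, the text says: "Several algorithms will be developed for the diagnosis of lentigo maligna in consecutive head / neck injuries".

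**Non-melanocytic subgroup.** It opens with "The subgroup of non-melanocytic malignant lesions should include consecutive cases defined as". The classes are "Carcinomatous neoformations with histological diagnosis of basal cell carcinoma", the same for squamous cell carcinoma, a list of benign histologies that includes nevi, and unbiopsied lesions that look benign clinically, on dermoscopy and on RCM. The main result is the rate of excised, histologically confirmed BCC by arm. The same accuracy measures are planned.

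**The concern.** Most classes in both lists can be assigned only once histology is known, which is after the test has been read and the excision decision made. A series filtered in that way is not consecutive. Each list also has a hole: the head/neck list has no place for BCC, SCC or any malignancy other than melanoma, and the non-melanocytic list has no place for melanoma.

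Two things are at stake. The head/neck outcome is worded as a rate of malignant lesions, but its numerator can contain only melanoma. And errors across classes (a BCC or SCC read as lentigo maligna, a melanoma read as BCC) cannot appear in the accuracy tables, because those lesions are not in the set. The lentigo maligna algorithm and the BCC accuracy figures would then describe a narrower range of lesions than a clinician meets.

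**Working it through.** **Can the omitted lesions enter the trial?** Yes. Inclusion criterion 3 asks for at least one criterion of suspicion for a malignant tumour and is not limited to melanoma. The design section also refers to consecutive patients with suspected skin cancer.

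**Where do they go?**

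| Biopsied lesion | Head/neck list | Non-melanocytic list |
|---|---|---|
| Melanoma | class 1 | no class |
| BCC | no class | class 1 |
| SCC | no class | class 2 |
| Listed benign histology | class 2 | class 3 |

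**Size.** The protocol gives no subset size, diagnosis mix or accuracy figure for either set, so there is no stated figure to reproduce. The following is an illustration in which every input is assumed: 100 consecutive head/neck lesions, 10 melanomas (the lentigo maligna target), k BCC/SCC and 90 − k benign; sensitivity 0.90; specificity in benign lesions 0.85; f is the share of BCC/SCC correctly called not lentigo maligna.

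- Malignancy rate: 10/(100 − k) as listed; (10 + k)/100 with all lesions.
- Specificity: 0.85 as listed; [0.85(90 − k) + f·k]/90 with all lesions.
- Positive predictive value (PPV): 9/[9 + 0.15(90 − k)] as listed; 9/[9 + 0.15(90 − k) + (1 − f)k] with all lesions.

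For k = 10 and f = 0.50, specificity is (68 + 5)/90 = 0.811, and PPV goes from 9/21 = 0.429 to 9/26 = 0.346.

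| k | Rate as listed | Rate, all | Specificity, all (f = 0.50 / 0.85 / 0.95) | PPV as listed | PPV, all (f = 0.50 / 0.85 / 0.95) |
|---|---|---|---|---|---|
| 5 | 10.5% | 15% | 0.831 / 0.850 / 0.856 | 0.414 | 0.371 / 0.400 / 0.409 |
| 10 | 11.1% | 20% | 0.811 / 0.850 / 0.861 | 0.429 | 0.346 / 0.400 / 0.419 |
| 20 | 12.5% | 30% | 0.772 / 0.850 / 0.872 | 0.462 | 0.305 / 0.400 / 0.439 |

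Four results follow.
1. The malignancy rate as listed is too low for every k above zero.
2. Specificity falls, stays or rises according to whether f is below, at or above 0.85.
3. With lentigo maligna as target and the algorithm held fixed, a restored BCC or SCC can add a false positive but never a true positive. PPV therefore falls, or is unchanged if f = 1.
4. Sensitivity for lentigo maligna does not change, because no target lesion is added.

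**Non-melanocytic subgroup.** With B BCCs and m melanomas among N lesions, the rate is B/(N − m) instead of B/N. The numerator is complete and the denominator is cut. With an assumed 10 melanomas in 100 lesions, the rate is overstated by a factor of 100/90 = 1.11.

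**The case against.** Several points count against a stronger reading.

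- *A reader might infer that the planned accuracy is inflated.* The documents do not show this. For specificity, the direction depends on how BCC and SCC are read, and no section says they are harder to separate from lentigo maligna than benign lesions are. For PPV, it depends on the target. If any malignancy counts, the example with k = 10 and f = 0.50 gives (9 + 5)/26 = 0.538, above 0.429.
- *A reader might infer that the hardest misclassifications are dropped.* The distinction that the Background calls difficult, benign against malignant lentigo, is kept in the head/neck list.
- *A reader might infer that both malignancy rates are wrong.* The second subgroup's main result is a BCC rate, and its numerator is complete.
- *Not every class rests on final diagnosis.* The unbiopsied classes are set by appearance.
- *No data are lost.* A facial BCC fits the second subgroup, melanomas count in the main randomised comparison, and the Data collection section requires a coded diagnosis for every excised lesion.
- *One Secondary Objective asks only about lentigo maligna against benign facial macules*, and the restriction largely fits that question.
- *The Background's remark that BCC is the commonest malignancy* concerns the general population and does not give its share among these macules.

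All of this limits the point without removing it. A separate Secondary Objective asks for the diagnostic accuracy of lentigo maligna without that restriction, and the algorithms are to be built on consecutive head/neck lesions. Renaming the head/neck outcome as a melanoma rate would cure the label but not the accuracy tables. Nor can this be left to an analysis plan, since the protocol fixes an explicit list that conflicts with its own outcome wording.

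A neighbouring gap is separate: unexcised lesions that are not clearly benign have no class, and the unbiopsied class requires RCM, which the control arm does not receive.

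**Conclusion.** The point holds. Both subsets are described as consecutive but defined largely by final histology, through closed lists that omit BCC and SCC in one and melanoma in the other. Read as written, the head/neck rate of malignant lesions is a melanoma rate and is too low whenever a head/neck macule proves to be BCC or SCC. In the non-melanocytic subgroup, a melanoma read as BCC cannot count as a false positive, and the denominator of the BCC rate is cut.

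Accuracy for lentigo maligna and BCC is thus estimated on a range of lesions selected after the test. Specificity may be biased in either direction. PPV for lentigo maligna as target can only be overstated or unchanged. The size cannot be derived from the protocol: the gap between 10.5–12.5% and 15–30% rests on the assumed 10 melanomas and 5 to 20 BCC/SCC per 100 lesions, and would vanish if no such lesion were enrolled. The effect is on secondary subsets and the algorithms drawn from them, not on the main randomised comparison of melanoma detection.

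**What to change.** - Define the head/neck subset by anatomical site and flat macule, as recorded at the index visit.
- Compute BCC accuracy on all enrolled lesions, or on an index-visit definition that does not exclude lesions suspected of melanoma. Restricting it to lesions suspected of being non-melanocytic would drop BCCs first suspected as melanoma, and the trial enrols patients with lesions suspicious of melanoma.
- Keep every lesion that meets the definition, whatever its final diagnosis, and add an other-malignancy class to each list.
- State the target for each measure: all malignancies for the head/neck malignancy rate, lentigo maligna/melanoma for the lentigo maligna algorithm, and BCC for BCC accuracy.
- Report melanomas read as BCC separately.
- Keep lentigo maligna against benign macules as the analysis for the Secondary Objective that asks exactly that.

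The cost is revised wording and one index-visit field, with no extra patients or procedures. Some accuracy figures may come out slightly less favourable.

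### In the head/neck and non-melanocytic subsets, RCM helps define which unbiopsied lesions are benign, so RCM sensitivity and negative predictive value are biased upward and subset membership depends on arm

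*Protocol*

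**What the plan says.** All of this is in the Protocol, mainly under Design and description of the study.

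- **Head/neck subset.** Three classes are listed: melanoma on histology, benign macules on histology, and "Benign macules not subjected to biopsy and with clear and defined parameters of clinical, dermoscopic and confocal microscopy benignity".
- **Non-melanocytic subset.** Carcinomas enter on histology. Benign lesions enter on histology or as "Benign neoformations not subjected to histological analysis and with clear and defined parameters of clinical, dermoscopic and RCM benignity".
- **Accuracy analyses.** For each subset, "Sensitivity, specificity, diagnostic accuracy, odds ratios (OR) with the 95% confidence interval will be evaluated". For the head/neck subset, predictive values of individual parameters and diagnostic algorithms are added, and "RCM features will be systematically analyzed to distinguish lentigo maligna from benign facial lentigos". Secondary Objectives asks for the accuracy of RCM in basal cell carcinoma and for the RCM features that separate lentigo maligna from benign facial macules.
- **Arm comparisons.** For head/neck lesions, "The main outcome will be the rate of malignant lesions identified within the" RCM arm, compared with the control arm. For the other subset, "The main result is to evaluate the rate of histologically confirmed, excised basal cell carcinomas detected in the" RCM arm, again against control.
- **Who gets histology.** In the RCM arm, "A clinical decision (removal or digital dermoscopic follow-up) will be made based on the RCM evaluation". In the control arm, clinicians "will make a clinical decision (removal or digital dermoscopic follow-up) without RCM evaluation".
- **Follow-up.** Lesions not removed are monitored for at least 6 months and excised if dermoscopy shows significant change. Data collection records each later decision and a coded histological diagnosis after excision. Neither unbiopsied class mentions the follow-up outcome.

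**The concern.** Two separate problems follow from these definitions.

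The first is circularity. RCM is the test being evaluated, it decides in its own arm who is excised, and it is part of the label given to lesions that are not. A tumour that looks benign clinically, dermoscopically and on RCM, and is never excised, is entered as a correct RCM negative. The resulting bias flatters RCM on the error that matters most for safety, the missed tumour. An algorithm developed on these labels would be trained partly on its own predictor.

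The second is that entry differs by arm. The unbiopsied benign classes require an RCM finding, and control lesions have none. A lesion left in place can join the subset in one arm and not in the other, on the basis of something observed after randomisation. Randomisation then no longer protects the comparison of malignancy rates within the subset.

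**Working it through.** The protocol states no RCM sensitivity, RCM specificity or biopsy share for these subsets, so there is no planned figure to reproduce. The calculations below are illustrations.

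**1. Accuracy.**

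Assumed inputs: true sensitivity Se of 0.85, 0.90 or 0.95; true specificity 0.70; a share u of RCM-negative lesions unbiopsied and classed benign, the same share among missed tumours as among benign lesions.

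Only biopsied misses count as false negatives, so:

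observed Se = Se / [Se + (1 − Se)(1 − u)]

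For Se = 0.90:
- u = 50%: 0.90 / (0.90 + 0.05) = 0.947
- u = 80%: 0.90 / (0.90 + 0.02) = 0.978
- u = 100%: 0.90 / 0.90 = 1.000

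If follow-up leads to excision of half of the unbiopsied misses, replace (1 − u) by (1 − u/2):
- u = 50%: 0.90 / (0.90 + 0.075) = 0.923
- u = 80%: 0.90 / (0.90 + 0.06) = 0.938
- u = 100%: 0.90 / (0.90 + 0.05) = 0.947

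| True Se | Observed at u = 50 / 80 / 100% | Same, half of misses recovered |
|---|---|---|
| 0.85 | 0.919 / 0.966 / 1.000 | 0.883 / 0.904 / 0.919 |
| 0.90 | 0.947 / 0.978 / 1.000 | 0.923 / 0.938 / 0.947 |
| 0.95 | 0.974 / 0.990 / 1.000 | 0.962 / 0.969 / 0.974 |

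For the other measures, take 1000 lesions at 14% prevalence (the melanoma percentage that Statistical analysis expects in the RCM arm, borrowed only as a convenient value) with Se = 0.90. There are 140 malignant lesions (126 RCM-positive, 14 RCM-negative) and 860 benign (258 RCM-positive, 602 RCM-negative).
- Negative predictive value: true 602/616 = 97.7%; at u = 50%, (602 + 7)/616 = 98.9%; at u = 100%, 616/616 = 100%.
- Specificity: true 602/860 = 0.700; at u = 50%, 609/(609 + 258) = 0.702; at u = 100%, 616/(616 + 258) = 0.705.

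Relabelling therefore acts on sensitivity and negative predictive value and hardly on specificity.

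**2. Arm comparison.**

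Assumptions: equal true prevalence p in both arms, all tumours excised in both arms, the subset used as denominator, all benign RCM-arm lesions retained, and a share f of benign control lesions unbiopsied and so not admitted.

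control rate = p / [p + (1 − p)(1 − f)]; RCM-arm rate = p

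With p = 7.3% (the control-arm melanoma percentage in Statistical analysis, again only for illustration):
- f = 5%: 0.073 / (0.073 + 0.881) = 7.7%
- f = 10%: 0.073 / (0.073 + 0.834) = 8.0%
- f = 20%: 0.073 / (0.073 + 0.742) = 9.0%

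At p = 14% the same shares give 14.6%, 15.3% and 16.9%. With f = 0 there is no distortion. The spurious difference makes the control arm look richer in malignancy, so it works against RCM.

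**The case against.** Several points on the other side are sound and limit the finding.

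- **Not every RCM-negative lesion becomes a true negative.** Both classes also require clinical and dermoscopic benignity. A lesion left in place that fails either part falls in no class.
- **Sensitivity of 100% is a ceiling, not a result.** A reader might infer that a missed tumour can never count as a false negative. But followed lesions may be excised later, the histology is recorded, and the histological classes carry no time limit. The upper values above apply only if every RCM-negative lesion is unbiopsied, classed benign and never excised afterwards.
- **Single RCM features behave differently from the overall reading.** Their sensitivity among histologically proven melanomas is not forced towards 100%. Those melanomas are still selected in part by the RCM-based decision.
- **Specificity is not made meaningless.** One might argue that, because enrolment requires a suspicious lesion, no lesion can be clearly benign and only excised lesions remain. Inclusion criterion 3 asks for at least one such lesion per patient, and Data collection provides for several lesions per patient, so the unbiopsied classes need not be empty.
- **The arm effect may be small.** The protocol expects that control patients will likely need immediate biopsy, and it does not state the denominator of the rates. If all lesions or all patients are the denominator, this effect disappears.

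None of this removes the core problem. Follow-up is planned, but uneventful follow-up is not a condition of benign status, and RCM is. The control pathway explicitly allows follow-up instead of removal, so some unbiopsied control lesions must be expected.

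**Conclusion.** The point holds for these two subsets and the secondary objectives that they serve. Followed exactly, the definitions bias RCM sensitivity and negative predictive value upward and make subset membership depend on arm.

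The size cannot be derived from the protocol. The range of about 0.95 to 1.00 for a true sensitivity of 0.90 (about 0.92 to 0.95 with half of the unbiopsied misses recovered) rests on the assumed biopsy shares and recovery. The arm effect rests on an assumed denominator and an assumed unbiopsied share among controls. It runs opposite to the accuracy bias and is minor if nearly all control lesions are biopsied.

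A reader might infer that the whole trial is compromised. The documents do not support that: the main comparison of excisions per melanoma, the sample size, and the chi-square and number-needed-to-excise analyses do not use the unbiopsied benign classes.

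**What to change.** 1. Define both subsets by baseline site and lesion type, for all enrolled lesions in both arms, whether or not they are excised.
2. Remove RCM from the definition of a benign lesion.
3. Take truth from histology for any lesion excised at any time; otherwise use the recorded outcome of the planned follow-up.
4. For lesions with neither, give best-case and worst-case bounds (all benign, all malignant).
5. Show beside this an analysis restricted to histologically verified lesions.

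The cost is modest. The two definitions are reworded. Histology and follow-up decisions are already recorded, and no procedure or clinical decision changes. Site and lesion type are not among the items listed under Data collection, so both must be recorded for every lesion. RCM sensitivity will read lower, with a wider interval. Dermoscopic follow-up is an imperfect reference and somewhat favours dermoscopy, which is why the histology-only analysis is needed; that analysis has its own selection, because RCM influences who is excised in its arm.
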